## Abstract

**Background:**

Smartphones enable the implementation of just-in-time adaptive interventions (JITAIs) that tailor the delivery of health interventions over time to user- and time-varying context characteristics. Ideally, JITAIs include effective intervention components, and delivery tailoring is based on effective moderators of intervention effects. Using machine learning techniques to infer each user’s context from smartphone sensor data is a promising approach to further enhance tailoring.

**Objective:**

The primary objective of this study is to quantify main effects, interactions, and moderators of 3 intervention components of a smartphone-based intervention for physical activity. The secondary objective is the exploration of participants’ states of receptivity, that is, situations in which participants are more likely to react to intervention notifications through collection of smartphone sensor data.

**Methods:**

In 2017, we developed the *A*ssistant to *L*ift your *L*evel of activit*Y* (Ally), a chatbot-based mobile health intervention for increasing physical activity that utilizes incentives, planning, and self-monitoring prompts to help participants meet personalized step goals. We used a microrandomized trial design to meet the study objectives. Insurees of a large Swiss insurance company were invited to use the Ally app over a 12-day baseline and a 6-week intervention period. Upon enrollment, participants were randomly allocated to either a financial incentive, a charity incentive, or a no incentive condition. Over the course of the intervention period, participants were repeatedly randomized on a daily basis to either receive prompts that support self-monitoring or not and on a weekly basis to receive 1 of 2 planning interventions or no planning. Participants completed a Web-based questionnaire at baseline and postintervention follow-up.

**Results:**

Data collection was completed in January 2018. In total, 274 insurees (mean age 41.73 years; 57.7% [158/274] female) enrolled in the study and installed the Ally app on their smartphones. Main reasons for declining participation were having an incompatible smartphone (37/191, 19.4%) and collection of sensor data (35/191, 18.3%). Step data are available for 227 (82.8%, 227/274) participants, and smartphone sensor data are available for 247 (90.1%, 247/274) participants.

**Conclusions:**

This study describes the evidence-based development of a JITAI for increasing physical activity. If components prove to be efficacious, they will be included in a revised version of the app that offers scalable promotion of physical activity at low cost.

**Trial Registration:**

ClinicalTrials.gov NCT03384550; https://clinicaltrials.gov/ct2/show/NCT03384550 (Archived by WebCite at http://www.webcitation.org/74IgCiK3d)

**International Registered Report Identifier (IRRID):**

DERR1-10.2196/11540

## Introduction

### Background

Mobile health (mHealth) and sensing technologies recently sparked excitement because of their capability to deliver large-scale personalized behavior change interventions at low cost [1], which can potentially reduce the disease burden associated with health behaviors, such as diet behavior, smoking, or physical inactivity [2]. Beyond passive monitoring of health behavior, smartphones and wearables collect a wealth of contextual information (such as time, location, communication logs, or physical activities) that can be used to tailor the delivery of interventions to participant states that increase the intervention’s likelihood of success. For example, an intervention could only be delivered at points in time when the participant is likely to change her or his behavior (state of opportunity) or is likely to engage with the intervention content (state of receptivity) [3]. mHealth apps that utilize this kind of dynamic tailoring are referred to as just-in-time adaptive interventions (JITAIs) [3].

During the development process of a JITAI, it is crucial to decide what key intervention components are needed to affect the desired intervention outcome and what information should be used to tailor the delivery of each component to participants over time [4]. The first question involves an empirical evaluation of single candidate intervention components. The second question involves identifying effective time-varying moderators that indicate in which situations the intervention component is or is not effective. Unfortunately, these decisions can hardly be informed by past research because traditional study designs (eg, randomized controlled trials) rarely evaluate single intervention components or time-varying moderators of intervention effects. To facilitate the development of JITAIs, Klasnja et al, therefore, proposed the microrandomized trial (MRT) [5].

The goals of an MRT are to quantify proximal (short-term) main effects of single intervention components, to investigate how these effects change over time, and to identify which contextual variables moderate the effects of single intervention components. MRTs use repeated randomization of participants to different versions, or presence and absence, of individual intervention components over time, which enables estimation of time-averaged main effects of single intervention components on proximal outcomes as well as time-varying effects and their contextual moderators. Results of an MRT can consequently inform the researcher which components to include in an optimized version of the intervention and how to adapt the delivery of each intervention component to maximize effectiveness.

Although MRTs are designed to accommodate contextual moderation, context is likely to be multidimensional —for example, not just time or location but rather the nexus of time and location (or other higher order interactions) define opportune moments for intervention. This limits the approach of investigating single variables as potential tailoring variables within MRTs. A potential way of overcoming this limitation is to train machine learning models that classify the participants’ latent *states* of intervention receptivity or vulnerability given a vector of high-resolution smartphone sensor data. Research on interruptibility, for example, demonstrated that models trained on smartphone sensor data successfully predict the quality and quantity of participants’ reactions to notifications on their smartphone [6-8]. Thus, this approach could allow to continuously model each participant’s state of receptivity (ie, the likelihood of engaging with an intervention) from a vast number of variables. Predictions of these models can in turn be used to inform intervention delivery of a JITAI.

In this paper, we describe the rationale and design of a 6-week MRT that evaluates main effects and moderators of 3 different intervention components (self-monitoring prompts, planning, and incentives) of the *A*ssistant to *L*ift your *L*evel of activit*Y* (Ally), a smartphone app to promote physical activity. Ally delivers interventions via an interactive text-based chatbot interface and simultaneously collects contextual data using the smartphone’s built-in sensors. We also report descriptive statistics from our remote recruiting process and baseline characteristics of participants.

### Objectives

To inform the evidence-based development of JITAI for physical activity, the described study has the following objectives:

To quantify main effects and interactions of main effects of 3 intervention components of Ally, an mHealth intervention for physical activity.To explore how the effects of intervention components are moderated by contextual factors and change over time.To collect a wide range of high-resolution smartphone sensor data to predict the participants’ states of receptivity.

## Methods

### Study Setting

This study is part of a research collaboration between the Center for Digital Health Interventions, a joint initiative of the Department of Management, Technology, and Economics at ETH Zurich and the Institute of Technology Management at the University of St. Gallen and the CSS insurance, a large health insurer in Switzerland. Data for this study were collected from October to December 2017 in the German-speaking part of Switzerland. The study is registered on ClinicalTrials.gov (NCT03384550) and was approved by the ethical committee of ETH Zurich.

### The Assistant to Lift Your Level of Activity App

The Ally app focuses on measuring and increasing walking, a popular and safe activity [9,10] that is known to have positive health effects independent of other types of physical activity [11]. Steps per day as an objective measure of walking can be obtained from the majority of commercially available smartphones with acceptable accuracy [12]. The Ally smartphone app tracks participants’ daily step counts and provides interventions to help participants reach daily step goals. It contains a dashboard that displays basic information such as the participants’ current step count and the step goal of the current day as well as an activity overview of the past 7 days (Figure 1). Ally runs on the common operating systems Android and iPhone operating system (iOS). On Android smartphones, Ally obtains all physical activity–related information from GoogleFit, a health-tracking platform developed by Google. On iOS smartphones, the same information is obtained from the HealthKit, an application programming interface for health apps provided by Apple. To obtain smartphone sensor data, we used EmotionSense, a framework to support smartphone-based data collection originally developed for experimental social psychology research [13].

Step goals are personalized and calculated daily for each participant based on the participant’s activity over the past 9 days employing the moving-window percentile-rank algorithm described by Adams et al [14]. This adaptive goal-setting algorithm sets the daily step goal to the sixtieth percentile of the participant’s step count distribution of the past 9 days, meaning that the participant reaches her or his step goal 40% of the times when maintaining her or his recent activity level. Previous studies demonstrated that this adaptive goal setting outperforms static step goals [14,15]. To facilitate maintenance of behavior change, adaptive step goals are capped at 10,000 steps per day, which approximates the World Health Organization recommendations for physical activity [16,17].

To administer the intervention components evaluated in this study, the Ally app includes a chatbot (Ally) that provides interactive coaching dialogues similar to other messaging apps such as Apple’s iMessage, Facebook’s Messenger, or WhatsApp. The open source behavioral intervention platform MobileCoach [18] was used to build the chatbot and deliver the interactive coaching dialogues. In previous studies, MobileCoach-based interventions have successfully reduced problem drinking in adolescents [19] and engaged the majority of participants of a 3-month smoking cessation program [20]. Participants interact with Ally by selecting predefined answer options (Figure 1) that trigger a response by the chatbot according to the conversational rules specified in the MobileCoach system.

Beyond specific interventions, the chatbot also communicates the daily step goal in the morning and feedback regarding the goal together with informative facts about physical activity at 8 pm in the evening to all participants.

### Study Design

From October to December 2017, insurees of a large Swiss health insurance used the Ally app over a 12-day baseline and a 6-week intervention period. During the baseline period, participants only had access to the dashboard of the app, and no interventions were administered. Over the course of the 6-week intervention period, we randomized participants to different versions of 3 intervention components: daily self-monitoring prompts (2 levels; within-subjects), a weekly planning intervention (3 levels; within-subjects), and daily incentives (3 levels; between-subjects). The rationale for these intervention components is described below. To meet study objective three, we aimed to explore if and how participants’ reaction to intervention components were dependent on their context. To do so, we ideally need to observe reactions to intervention notifications in a wide variety of contexts. We, therefore, sent out intervention and step goal–related notifications at random points in time but within prespecified time windows that guaranteed delivery at appropriate times. For example, daily step goal notifications were delivered at a random point in time between 8 am and 10 am as users likely expect to be notified about their goal early in the day. Participants completed a Web-based questionnaire at baseline and at postintervention follow-up and received CHF 10 (US $10 as of 2017) for the successful completion of both questionnaires. If participants provided consent, they were invited to participate in exit interviews after the end of the study that investigate perceptions of participants and mechanisms of behavior change.

The following subsections first describe details and rationale for each intervention component as well as for potential moderators. Subsequently, we outline how each component was randomized during the intervention period and how we define the proximal outcome to evaluate each component.

**Figure 1 figure1:**
[figure not shown]
The Ally app: Dashboard with daily (left) and weekly overview (middle) and chat interactions with the Ally chatbot (right).

### Intervention Components

#### Self-Monitoring Prompts

Self-regulatory processes have been identified as a key factor for health behavior change [21,22]. To support participants’ self-regulation, we designed short dialogue-based self- monitoring prompts. Self-monitoring prompts remind the participants of their daily step goal, compare the participants’ current step count to their daily goal, and provide an estimate of walking minutes necessary to reach the goal together with an actionable tip on how to increase physical activity. These dialogues were designed to support the 3 subprocesses of the self-regulatory construct action control, namely self-monitoring, awareness of goals or standards, and self-regulatory effort [23,24]. If a participant had already reached their daily step goal when starting the dialogue, she/he would receive positive and encouraging feedback from the Ally chatbot instead.

Participants were randomized to receive a self-monitoring prompt or no prompt every day during the intervention period except Sunday, as this day was reserved for the planning intervention (see below). Self-monitoring prompts were delivered at a random point in time between 10 am and 6 pm.

Participants’ general tendency to self-monitor their physical activity may affect the effect of self-monitoring prompts because the information provided by the prompt is likely to be redundant to participants who are already aware of their activity level. In addition, timing of the self-monitoring prompt may be critical. Research from cognitive psychology demonstrates that people assign more value to performance increases when their current performance is close to their goal [25]. Consequently, self-monitoring prompts may be more effective if they are sent at times when participants are closer to reaching their step goal.

#### Planning

Even if motivation to change exists, previous studies show that on average, 47% of people fail to act upon their good intentions [26]. Forming specific plans about when and how to act increases the likelihood of performing the intended behavior [27,28] and helps to bridge the so-called intention behavior gap. Planning can be further divided into action planning (AP; specifying when, where, and how to act) and coping planning (CP; specifying coping responses for barriers and difficult situations) [29]. Plans that are articulated in an if-then format (eg, “if I am tired at work, I will go for a brief walk to get new energy”) are typically referred to as implementation intentions [30].

Every Sunday during the intervention period, participants received either an AP, a CP, or no planning intervention (control; CC). In the AP condition, Ally asks the participant to plan at least one and up to 3 walks for the upcoming week. To plan a single walk, the participants need to specify the day of the week, the time, and the route that they intend to walk. To create flexible plans and thus increase the likelihood of adherence, Ally advises the participant to choose event-related times (eg, after work) instead of actual times. In the CP condition, Ally asks the participant to identify barriers for physical activity by reflecting on the 2 least active days from the previous week. The participant is then prompted to develop counterstrategies for each barrier using the if-then format of implementation intentions [30]. Ally guides this process using examples for common barriers for physical activity that have been identified in previous studies [31-33], for example: “If I want to go for a walk but I lack motivation, I will think of the benefits of walking for health to motivate myself.” Finally, the participant has the option to anticipate days of the upcoming week where the barrier may arise again. Both AP and CP include reminders for the participant on days when either a walk or a coping reaction was scheduled. To address the third objective of this study, planning interventions were sent out on Sundays at a random point in time between 10 am and 8 pm.

Participants’ activity level and contexts may moderate the effects of AP and CP. Participants with low activity levels may be more likely to benefit from AP, which promotes the initiation of action, whereas participants with high activity levels may benefit more from CP, which prevents routines from distraction [29,34]. Furthermore, completing the planning intervention can take several minutes and requires a considerable amount of the participants’ attention and cognitive capacity. Ideally, the planning intervention should, therefore, not be delivered in situations where the participant is involved in an attention-consuming activity, such as social activities or work.

#### Incentives

Meta-analyses [35,36] and recent randomized trials [37-39] have demonstrated the ability of financial incentives to increase physical activity. However, financial incentives may reduce intrinsic motivation [40,41]; thus, charity incentives have been proposed as an alternative incentive strategy. Charity incentives, that is, donations to a charity organization, could foster experiences of autonomy and relatedness, which are known to facilitate rather than impede the buildup of intrinsic motivation [42]. Moreover, 2 recent studies have so far compared financial and charity incentives with mixed results [37,43].

In this study, participants were randomly allocated to either a financial incentive, a charity incentive, or a control condition using an allocation ratio of 1:1:1. In the financial incentive condition, participants received CHF 1 (US $1 as of 2017) for each day they met their personalized step goal. In the charity incentive condition, instead of keeping the reward to themselves, participants made a donation of CHF 1 to a charity of their choice. Participants allocated to the control condition received no incentives. Earned rewards (maximum of CHF 42) were paid to participants or donated to charity after completion of the study.

We hypothesize that the presence of incentives moderates the effect of the other intervention components. Both planning and self-monitoring prompts target the participants’ self-regulatory processes and thus require the participant to be motivated to reach the provided step goals to produce an effect [44]. As we expect the incentives to increase the motivation of participants, we hypothesize that effects of self-monitoring prompts and planning are more pronounced for participants receiving financial or charity incentives.

### Randomization, Allocation Concealment, and Blinding

The MobileCoach version used in this study requires the time point of dissemination for all dialogues to be known a priori. Therefore, randomization had to be performed upon enrollment of participants for all intervention components. Each participant was randomized to 1 out of 3 incentive conditions using simple randomization and an allocation ratio of 1:1:1. In addition, participants were randomized to 1 out of 9 planning intervention sequences (S_1_-S_9_) that determine the order in which the participant received the AP intervention, the CP intervention, or CC intervention throughout the intervention period. We used blocked randomization with a block size of 9 to achieve balance between the sequences. The resulting intervention schedule (Table 1) is uniform and strongly balanced, which controls for time and carry-over effects [45]. To avoid interference of self-monitoring prompts and planning, self-monitoring prompts were not delivered on Sundays. Thus, subtracting 6 from 42 left 36 available days for delivering self-monitoring prompts. To prevent repetition of content, we created 18 different versions of self-monitoring prompts that we randomly allocated to the 36 days for each participant. Consequently, at each of the 36 days, half of participants received a self-monitoring prompt (on average), whereas the other half received no prompt. All randomizations were performed using random number sequences generated with the shuffle-array package in JavaScript.

The fully automated randomization process guarantees allocation concealment for everyone involved in the study. Variables in the dataset indicating intervention allocation are encrypted to blind members of the research team involved in data analysis. A researcher at the Swiss Federal Institute of Technology in Zurich who is not involved in data analyses holds the decryption key and is instructed to safely store the key until the analysis script has been finalized. Due to the setting of the study, it is not possible to blind participants to intervention assignments. To reduce the impact of performance and attrition bias, participants were not informed about the details of the intervention components before the study.

### Measurements

#### Primary and Secondary Outcomes

As the intervention components (see Table 2) are randomized on different timescales, we need to define primary and secondary proximal outcomes that correspond to these timescales to correctly evaluate the intervention components. The proportion of overall participant days that step goals are achieved during the intervention period is the primary outcome to evaluate the different incentive conditions. Weekly and daily proportions of participant days that step goals are achieved during the intervention period are the primary outcomes of the planning and self-monitoring prompts, respectively. On the same timescales, differences in steps per day measured with the smartphone are investigated as a secondary outcome.

**Table 1 table1:** Intervention schedule of the planning intervention.

Sequence	Week 1	Week 2	Week 3	Week 4	Week 5	Week 6
S_1_	AP^a^	AP	CP^b^	CC^c^	CC	CP
S_2_	CP	CP	CC	AP	AP	CC
S_3_	CC	CC	AP	CP	CP	AP
S_4_	AP	CP	CP	AP	CC	CC
S_5_	CP	CC	CC	CP	AP	AP
S_6_	CC	AP	AP	CC	CP	CP
S_7_	AP	CC	CP	CP	CC	AP
S_8_	CP	AP	CC	CC	AP	CP
S_9_	CC	CP	AP	AP	CP	CC

^a^AP: action planning.

^b^CP: coping planning.

^c^CC: control condition (no planning).

**Table 2 table2:** Overview of intervention components of the *A* ssistant to *L* ift your *L* evel of activit*Y* (Ally) app.

Component and intervention options		Randomization	Mode of delivery	Time of delivery	Behavior change techniques [48]^a^	Proximal outcome

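### For incentives, the primary outcome is scored against a goal that resets to each participant's last 9 days, so a sustained step gain largely drops out of it; planning is attenuated by a quarter to a third, prompts hardly at all

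*Protocol article*

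**What the plan says.** Under Primary and Secondary Outcomes, the incentive outcome is given as: "The proportion of overall participant days that step goals are achieved during the intervention period is the primary outcome". For the other two components, planning and prompts: "Weekly and daily proportions of participant days that step goals are achieved during the intervention period are the primary outcomes of the planning and self-monitoring". Steps come second: on the same timescales, "differences in steps per day measured with the smartphone are investigated as a secondary outcome".

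The goal itself is defined in the section on the Ally app. The algorithm "sets the daily step goal to the sixtieth percentile of the participant’s step count distribution of the past 9 days", it is recalculated every day, and it may not exceed 10,000 steps. The section spells out the consequence: a participant "reaches her or his step goal 40% of the times when maintaining her or his recent activity level".

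Incentive arm is assigned once, between subjects, for all 42 days. Planning condition changes weekly within subject (Table 1). Prompts vary daily within subject. The Sample Size section simulates gains in attainment of .05, .10 and .15 for the incentive and planning main effects and for their interaction. Its text mentions no feedback from a gain into the goal.

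**The concern.** The yardstick moves with the behaviour it measures. Once a participant has walked more for 9 days, every day in the goal window is a day at the new level, and the protocol's own statement puts attainment back at about 40%. A between-subject component that is present on all 42 days is the most exposed, because its treated participants are soon compared with their own improved selves.

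The Conclusions of the Abstract and the Discussion say that components found efficacious will enter a revised app. A null on attainment for incentives could be read as no effect on walking, and equal attainment in the financial and charity arms as equal benefit. Neither reading would be safe.

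**Working it through.** **Inputs from the article.** Goal: 60th percentile of the previous 9 days, cap 10,000. Baseline 12 days, intervention 42 days. Baseline steps: mean 6336, between-person SD 2701. Assumed gains in attainment: .05 to .15. Planning sequences: Table 1.

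**Assumptions not in the article.** Within-person SD 2000 to 4000 steps, or within-person CV .30 to .60; normal or lognormal days; autocorrelation 0 or 0.3.

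**Step 1: reproduce the 40%.** Take the goal as the 6th of 9 ordered days. If all ten days are exchangeable, the new day exceeds it when it ranks 7th to 10th of ten: 4/10 = .40. Simulation gives .400 (.419 with an interpolated percentile). The stated figure holds.

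**Step 2: incentives, sustained gain, no cap.** On intervention day 1 none of the 9 window days carries the gain, on day 2 one does, and from day 10 all nine do. If the effect shrinks in proportion, the share kept over 42 days is

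(9 + 8 + … + 1)/9 ÷ 42 = 5/42 = 11.9%.

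Simulation with the shift set to be worth +.15 agrees:
- fixed baseline goal: +.140 as realised over 42 days
- moving goal: +.016, a share of .016/.140 = 11%
- by week on the moving goal: .092, .006, then zero in weeks 3 to 6

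Autocorrelation of 0.3 lifts the share to 13.5% at most.

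**Step 3: the same with the 10,000 cap.** Participants whose goal reaches the cap face a fixed target, so some effect persists.

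| Gain of +1000 steps/day | Fixed goal | Moving goal | Kept |
|---|---|---|---|
| Capped, SD 2000 | .181 | .045 | 25% |
| Capped, SD 3000 | .125 | .035 | 28% |
| Capped, SD 4000 | .097 | .030 | 31% |
| Capped, CV .30 to .60, lognormal | .15 to .24 | .026 to .046 | 17% to 19% |

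Over gains of 500 to 1500 steps and all these variants, the share kept is roughly 17% to 33%.

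**Step 4: goal-directed response.** Suppose incentives make participants top up to that day's goal on 10% to 25% of the days on which they would have fallen short. The 42-day effect is then +.038 to +.101, and about +.035 to +.09 in weeks 3 to 6. The effect lasts. But a 10% top-up, worth only about 100 to 190 steps/day, scores about .038 with the cap, much the same as the .026 to .046 from a sustained +1000.

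**Step 5: planning.** Over the 7 days of a week the same linear argument keeps (9 + 8 + … + 3)/9 ÷ 7 = 42/63 = 67%. Simulation on Table 1, with the gain lasting its own week:
- no cap: .031, .062 and .093 against .047, .094 and .140 with a fixed goal, about 67%
- cap: 73% to 76%
- carry-over: in the no-cap run at +.15, control weeks fall to .368, because they inherit a goal raised by earlier planning weeks

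**Step 6: prompts.** The goal for the day is set before the prompt arrives. Effects of .049, .094 and .141 remain, practically the full size.

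**Step 7: what this does to power (illustration).** 220/3 ≈ 73 per arm; 73 × 42 = 3066 person-days, treated as independent, which is optimistic:
- .40 vs .55: power about 1.00
- .40 vs .416 (sustained gain, no cap): about .25
- .448 vs .483 (+1000 steps, SD 3000, cap): about .79

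**The case against.** The strongest defence is that attainment is the right proximal outcome. The app exists to help people reach their daily goals, and the financial arm is paid for each day the goal is met. Topping up to that day's goal is therefore a natural mechanism, and under it the effect does not vanish. That stands, and it means the loss in Steps 2 and 3 depends on mechanism. It does not rescue attainment as a ranking of walking gain (Step 4).

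Steps per day is already a planned secondary outcome with the same model. That also stands: the information is not lost, only placed second.

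A reader might go further in four ways that the document does not support:
- *Planning effects are erased as well.* They are not; about two thirds to three quarters is kept. If planning gains never fade, the contrast is small against a frozen goal too (about .03 at +.15), which comes from the crossover and not from the goal.
- *Incentive arms look like control after day 9, and a sustained gain scores the same as one confined to the last 14 days.* Both hold only without the cap. With it, some difference persists, and in a capped run sustained, last-14-day and first-14-day gains score .034, .024 and .007.
- *The Sample Size section is contradicted.* Its constant main effects of .15 are held fixed across the plotted scenarios; it does not claim constancy over days. The feedback merely does not appear to be reflected there.
- *The primary outcome must be replaced.* Data collection is complete, so a swap invites an outcome-switching objection.

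**Conclusion.** The point holds as a limit on what the incentive comparison can show. For a sustained gain that does not chase the goal, roughly 10% to 12% of the fixed-goal effect reaches the primary outcome without the cap, and roughly 17% to 33% with it. For a goal-chasing response, about +.04 to +.10 persists, at a small gain in steps. Attainment therefore cannot order the incentive conditions by walking gain, and a null on it does not show absence of a gain. Planning estimates are attenuated by about a quarter to a third and carry over between weeks through the goal. Prompts are sound on this point.

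The 40% and the 9-day mechanism come from the article. The exact shares rest on the assumed within-person variability and on the form of the response, neither of which the article gives.

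**What to change.** Keep the prespecified primary outcome. Before the allocation variables are decrypted:

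1. State that a null or equal result on adaptive attainment for incentives is not evidence of no, or equal, effect on walking.
2. Base the incentive conclusion and the decision on components jointly on attainment and the steps-per-day analysis already planned.
3. Add a supportive analysis of attainment against a goal frozen at baseline (60th percentile of the last 9 baseline days, same cap), and describe the planning estimate on the adaptive goal as attenuated.

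The timing allows it: the article says that analyses start only after its publication and that the decryption key is held back until the analysis script is final. No new data are needed. The cost is one extra analysis, for which Table 4 shows baseline steps missing in 76 of 274 participants (27.7%), and a primary conclusion that is less simple to state.
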